#### 2.11.3. Follow-Up of Outcomes (12 Weeks Post-Intervention)

We will use two-level hierarchical linear and logistic regression models to investigate the change in primary and secondary outcomes 12 weeks after ending the PRET programme (T3-T4). Time varying variables (medication use and physical activity) will be included as covariates. We will explore if results differ based on group characteristics (age, sex, level and aetiology of ID) by adding them subsequently to the linear and logistic regression models.

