## Abstract

Progressive resistance exercise training (PRET) reduces cardiovascular risk factors (CVRF) in the general population. It is unknown if PRET also reduces these risk factors in adults with intellectual disabilities (ID). The aim is to present the protocol of an intervention study that investigates the effect of PRET on CVRF in adults with ID. We will use a repeated time series design with one study group. Adults with mild-to-moderate ID and at least two CVRF are eligible (Netherlands Trial Register, NL8382). During a 12-week baseline period, measurements take place at a 6-week interval. After this, the PRET programme starts for 24 weeks, after which all measurements will be repeated. We will use hierarchical regression models, adjusted for sport activity and medication use, to estimate the effect of PRET. After the intervention, the participants will be followed-up for 12 weeks. We will evaluate factors for successful implementation of exercise in daily life. Primary outcomes are: hypertension, obesity, hypercholesterolemia, diabetes, metabolic syndrome. Secondary outcomes are: physical fitness, sarcopenia, physical activity, activities of daily living, falls, challenging behaviour. If our results show that the PRET programme is effective, it may be a promising non-pharmacological intervention to reduce CVRF in adults with ID.

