Due to low physical activity levels [15], adults with ID are prone to other health problems. Low levels of physical activity can result in loss of muscle strength and muscle mass which can lead to sarcopenia at older age [16]. Sarcopenia is characterised by progressive and generalised loss of skeletal muscle mass and strength with a risk of adverse health outcomes [17]. Sarcopenia has been found prevalent in older people with ID, at already younger ages than in the general population [17,18]. In the general population resistance training reduces sarcopenia [19], as it increases the muscle strength and muscle mass [20]. Other studies showed that people with ID have poor balance, strength, muscular endurance, and gait speed [15,21] which can lead to difficulties in performing activities of daily living and thereby increase the dependency of caregivers [22] and falls. In addition to these health problems, challenging behaviour, such as aggression and self-injury, is common [23]. Team sports seem to reduce challenging behaviour [24], but it is still unknown if resistance training is effective in reducing challenging behaviour in adults with ID.

A PRET programme may enhance physical activity and be beneficial for people’s cardiovascular risk profile and health in general. In a previous study, we composed a Resistance Exercise Set for adults with ID (RESID) [25]. We found that these exercises were feasible to perform by adults with mild to moderate ID and CVRF [26]. Therefore, the RESID can be used in the PRET programme as the content of the training sessions. This programme may be an additional intervention to existing pharmacological treatments for CVRF in adults with ID. To our knowledge, no study investigated the effect of PRET on reducing the above-described health issues in this population. The primary aim of this study is to investigate the effect of the PRET programme on CVRF (hypertension, obesity, hypercholesterolemia, diabetes, and metabolic syndrome) in adults with ID. Second, we will investigate the effect of PRET on physical fitness, sarcopenia, physical activity, activities of daily living, falls, and challenging behaviour. This paper presents the study protocol, outcomes, and statistical analysis plan.

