#### 2.7.3. Physical Activity

To assess the physical activity levels, we will use the International Physical Activity Questionnaire (IPAQ) [39]. The IPAQ assesses daily physical activity over the last seven days. The IPAQ consists of 27 items that are divided into five domains of physical activity: job-related, transportation, housework, leisure time, and sitting. For each domain, scores are provided for walking, moderate-intensity activities, and vigorous-intensity activities. Scores will be reported as the estimation of metabolic equivalent-minutes per week (MET-minutes/week) [40]. The IPAQ has been found reliable and valid in the general population [39].

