### 2.10. Procedures

Figure 1 shows a schematic representation of the study procedures. Participant characteristics will be collected at T0. During the 12-week baseline period, measurements for the primary and secondary outcomes will take place at six-week intervals (T0, T1, and T2). A minimum of three measurements is needed to establish a valid baseline and to filter out the natural variability that may exist in these parameters without applying any intervention [49]. We will record changes in sport activities and medication use related to CVRF. The falls will be tracked continuously throughout the 12-week baseline period.

After the baseline period, the intervention period starts for a duration of 24 weeks. We will record changes in sport activities and medication use related to CVRF. At the end of the intervention period all measurements for the primary and secondary outcomes will be repeated (T3).

The follow-up period will last 12 weeks. Directly post-intervention, we will ask all participants to fill out a questionnaire about their experiences with the PRET programme. We plan interviews with participants and their trainers who want to continue the PRET programme and evaluate facilitators and barriers for successful exercise in their daily life. At the end of the follow-up period all measurements for the primary and secondary outcomes will be repeated (T4). Falls will be tracked continuously throughout the follow-up period. Participants who drop out prematurely from the intervention, will be invited for the measurements at T3 and T4.

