#### 2.11.2. Effect of PRET Programme (Post-Intervention)

We will use two-level hierarchical linear and logistic regression models to investigate the effect of the PRET programme at the end of the intervention period (T3). The first level consists of the repeated measurements nested within a participant; the second level consists of the clustering of participants by the trainer delivering the PRET programme. We will use the likelihood ratio test (correcting for the boundary) to assess the necessity for random coefficients in the regression model. Statistical analyses will be performed with R-statistics (R Foundation for Statistical Computing, Vienna, Austria) and we will use the package Linear and Nonlinear Mixed Effects Models (nmle) [50]. A two-tailed significance level of 0.05 will be used for all tests.

The variables for the PRET programme will be coded as 0 (baseline period at T0, T1, and T2) or 1 (intervention period T3). To check the assumption of stable baseline measurements, we will investigate the effect of time on each outcome variable assessed during the baseline period. Time varying variables (changes in sport activities and medication use related to CVRF) will be included as covariates in all models.

We will use the data from all participants who started the study. We will also analyse the effect of the intervention for participants who completed the intervention as planned.

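### The T3-T4 follow-up model adjusts for physical activity, which is itself a secondary outcome and a likely consequence of the training stopping, and its covariate differs from that of the T3 effect model

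*Protocol article*

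**What the plan says.** Section 2.11.3 sets out to model "the change in primary and secondary outcomes 12 weeks after ending the PRET programme (T3-T4") with two-level linear and logistic regression. On adjustment it states: "Time varying variables (medication use and physical activity) will be included as covariates". It makes no exception for any outcome.

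The abstract lists activity among the outcomes: "Secondary outcomes are: physical fitness, sarcopenia, physical activity, activities of daily living, falls, challenging behaviour". Section 2.7.3 gives the instrument: "To assess the physical activity levels, we will use the International Physical Activity Questionnaire (IPAQ"), a recall of the last seven days that includes leisure-time and vigorous activity. The Introduction expects the training to act on it: "A PRET programme may enhance physical activity and be beneficial for people’s cardiovascular risk profile and health in general".

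For the effect at T3, section 2.11.2 names another covariate and claims wider reach: "Time varying variables (changes in sport activities and medication use related to CVRF) will be included as covariates in all models".

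Section 2.10, in its account of the follow-up period, adds: "We plan interviews with participants and their trainers who want to continue the PRET programme".

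**The concern.** A covariate measured after treatment, and affected by it, is not a confounder of the change being estimated. Section 2.11.3 asks what happens to the outcomes in the 12 weeks after the programme ends. One of the first things likely to happen is that activity falls, because the sessions stop. Holding activity constant then answers a different question: how outcomes would change if activity did not.

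At stake is how the follow-up result is read. If part of the post-training loss runs through lower activity, the adjusted change looks smaller than the loss participants actually experience, and the gains look more durable than they are. For the activity outcome itself, the stated model carries no information. Because the T3 model adjusts for something else, the T3 effect and the T3-T4 change are also not on the same footing.

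**Working it through.** The plan gives no figure for the T3-T4 analysis (the sample size in section 2.12 concerns HbA1c), so there is nothing to reproduce. The check is a comparison of the sections, followed by an illustration with assumed inputs.

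**1. Activity as outcome and covariate.** Let Y be the IPAQ score and let the model be Y = a + b·time + g·activity. With activity equal to Y, the fit is g = 1, a = 0, b = 0. A numerical check with a true mean change of -0.50 SD returned a coefficient of 1 and an estimated change of 0. This is algebra and needs no assumption beyond a literal reading of 2.11.3.

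**2. Activity on the path for other outcomes.** Section 2.5 bars participants from starting another activity to raise their activity level during the study period. Section 2.1 counts the follow-up as part of that period. The main foreseeable source of a T3-T4 change in activity is therefore the training stopping or continuing. Because the IPAQ looks back seven days, the T3 score can include the training sessions themselves.

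**3. Illustration when everyone stops.** All inputs are assumed and in SD units: stopping lowers activity by 1; it worsens the outcome directly by d = 0.50; each SD of activity lost adds b.
- True change = d + b × 1.
- Change adjusted for activity = d.

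| b | True worsening | Adjusted | Understated by |
|---|---|---|---|
| 0 | 0.50 | 0.50 | 0 |
| 0.25 | 0.75 | 0.50 | 0.25 (33%) |
| 0.50 | 1.00 | 0.50 | 0.50 (50%) |

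**4. Illustration if some continue.** Further assumptions: a share c continues with no mean change in activity or outcome, b = 0.25, and the random variation in the activity change has SD 0.7 (variance 0.49). The true change is 0.75 in stoppers and 0 in continuers.
- Unadjusted pooled change = (1 - c) × 0.75.
- Adjusted pooled change = 0.50 × (1 - c) × 0.49 / [c(1 - c) + 0.49].

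| c | Unadjusted | Adjusted |
|---|---|---|
| 25% | 0.56 | 0.27 |
| 50% | 0.38 | 0.17 |
| 75% | 0.19 | 0.09 |

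Simulation gave the same values. Neither column describes stoppers or continuers, so adjusting for activity does not separate the two groups. The simple factor (1 - c) holds only for the unadjusted change.

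**5. The two covariate lists.** Section 2.11.2, the abstract, section 2.5 and the Discussion all speak of sport activities and medication. Only 2.11.3 says physical activity. Section 2.11.2 says its list applies in all models, so the two statements cannot both stand as written.

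**The case against.** The strongest reply is that physical activity in 2.11.3 is loose wording for sport activities, given that every other section uses the latter term. That is possible. But as written, 2.11.3 names a defined outcome of the study, so the text needs correcting on either reading. The substitution also would not cure the problem by itself: continued training could well be logged as a sport activity, and the adjustment would again be for a consequence of treatment.

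A second reply is that no analyst would report a model of activity on activity. Probably so, but that means departing from the plan. A third is that a change conditional on activity is a legitimate question. It is, if labelled as explanatory. A fourth is that a seven-day recall measures activity with error, so adjustment would remove less than the illustration shows. That stands, and is one reason the size cannot be stated.

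A reader might infer more than the article supports:
- **That every outcome is adjusted in this way.** Faller status is not; section 2.11.4 uses an unadjusted McNemar test.
- **That T4 is never set against baseline.** The same test compares the follow-up period with the baseline period. For the other outcomes, a condensed article need not list every contrast, so the silence is no error.
- **That the T3-T4 change is known to mix stoppers with continuers.** Section 2.10 speaks only of people who want to continue. It gives no number and does not say that training goes on before T4. Section 2.5 may already capture continuation among the recorded changes in sport activities.

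**Conclusion.** The concern holds in a limited form. Read literally, section 2.11.3 adjusts physical activity for itself and returns no change. For the other regression outcomes it adjusts for a likely consequence of the training stopping or continuing, which understates the loss if activity falls after T3 and affects the outcome. The direction rests on those two conditions. The size cannot be computed from the documents: the 0 to 50% understatement shown above follows from assumed inputs, and the shares continuing are assumed as well. The covariate also conflicts with section 2.11.2.

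The point concerns the follow-up analysis only. The primary comparison of T3 with T0-T2 does not use this covariate, so the documents give no reason to extend the criticism to it.

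**What to change.** - Make the T3-T4 change without physical activity, adjusted for medication use related to cardiovascular risk factors as in 2.11.2, the main follow-up estimate.
- Never adjust the activity outcome for itself.
- Reconcile the covariate wording of 2.11.2 and 2.11.3. If sport activity is kept, state that PRET sessions and their continuation do not count as sport activity. Copying the 2.11.2 list without this restriction could bring the same problem back.
- Label any activity-adjusted model as explanatory.
- As an addition from data already planned, report T4 against baseline (T0-T2) beside T4 against T3. A small T3-T4 change alone does not show that T4 is still better than baseline.
- If some participants continue PRET before T4, describe the change by continuation status. If the record of sport activities does not show this, one yes/no item at T4 would.

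The cost is a few lines of wording and slightly more analysis, with no extra visits or participants. Continuing is self-selected, so any split by continuation is descriptive only.

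### The T3-T4 follow-up models adjust for physical activity, which is itself one of their outcomes: its own change becomes zero by construction, and the other outcomes get a change net of activity, not the total change

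*Protocol article*

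**What the plan says.** Section 2.11.3 sets out to study the "change in primary and secondary outcomes 12 weeks after ending the PRET programme (T3-T4"), using two-level linear and logistic models. It then adds one covariate rule for all of them: "Time varying variables (medication use and physical activity) will be included as covariates". No outcome is exempted.

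Physical activity is on the outcome list. The Abstract states: "Secondary outcomes are: physical fitness, sarcopenia, physical activity, activities of daily living, falls, challenging behaviour". The Introduction repeats it as an aim: "we will investigate the effect of PRET on physical fitness, sarcopenia, physical activity, activities of daily living, falls, and challenging behaviour". Section 2.7.3 gives the instrument: "The IPAQ assesses daily physical activity over the last seven days". Section 2.10 schedules it at T3 and again at the last visit: "At the end of the follow-up period all measurements for the primary and secondary outcomes will be repeated (T4").

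Elsewhere the adjustment variable has another name. The Abstract says: "We will use hierarchical regression models, adjusted for sport activity and medication use, to estimate the effect of PRET". Section 2.11.2 and the Discussion also name sport activities with medication use, and section 2.5 has changes in those two recorded. Only 2.11.3 says physical activity.

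On what happens after T3, section 2.10 says: "We plan interviews with participants and their trainers who want to continue the PRET programme". It gives no share of participants who do so.

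**The concern.** Two problems follow from the one sentence.

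First, physical activity is both response and covariate in one of the models. That model cannot show a change in activity after supervised training stops, although this is one of the questions the follow-up period is there to answer.

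Second, for the remaining outcomes, activity at T4 is measured after the programme has ended and may have moved because it ended. Holding it fixed changes the question. The section asks how outcomes change over the 12 weeks; the model answers how they would change at an unchanged level of activity. Presented as the follow-up result, that figure could understate or overstate what happens to participants.

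**Working it through.** The plan states no figure for this analysis, so there is none to reproduce. The check is algebra plus a small simulation.

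**1. Physical activity on itself.** With PA for activity and t = 0 at T3 and 1 at T4, the literal model is

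PA = b0 + b1·t + b2·PA + error.

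The values b0 = 0, b1 = 0, b2 = 1 fit every observation exactly. A least-squares fit to 61 simulated participants with a raw T3-T4 change of -1.05 returned b2 = 1.000 and b1 = 0 to machine precision.

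**2. Other outcomes.** In a linear random-intercept model with both visits complete, once the activity slope g has been estimated,

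adjusted change = total change − g × d,

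where d is the mean shift in activity from T3 to T4. The adjusted and total changes therefore differ whenever g and d are both non-zero. The slope g mixes within-person and between-person association, so either can make it non-zero. Logistic models do not obey this exact identity, but they too estimate a change conditional on activity.

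**3. Simulation.** 60 replicates of 300 participants per scenario. All inputs are assumptions in arbitrary units, because the document gives none: between-person SD of activity 1 and of the outcome 1, within-person noise SD 0.3, higher outcome worse, and a fall in activity of 1 on stopping unless stated.

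| Scenario | Total change | Slope g | Mean shift d | Total − g × d | Fitted adjusted change |
|---|---|---|---|---|---|
| A. Half continue; stopping itself worsens the outcome by 0.5 | 0.253 | -0.207 | -0.5 | 0.253 − 0.104 = 0.149 | 0.149 |
| B. Nobody continues; outcome depends on activity (slope -0.5) | 0.496 | -0.509 | -1 | 0.496 − 0.509 = -0.013 | -0.010 |
| C. Nobody continues; activity unrelated to the outcome | 0.500 | 0.007 | -1 | 0.500 + 0.007 = 0.507 | 0.506 |
| D. Nobody continues; loss not through activity, but more active people have better outcomes | 0.498 | -0.324 | -1 | 0.498 − 0.324 = 0.174 | 0.172 |
| F. Nobody continues; activity rises by 0.5 and affects the outcome; stopping adds 0.8 | 0.554 | -0.504 | +0.5 | 0.554 + 0.252 = 0.806 | 0.804 |

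The column d is the planned mean shift; the small gaps between the last two columns are simulation noise. At the enrolment target of 61, A gave 0.253 → 0.150 and B gave 0.509 → 0.020.

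**4. Reading the table.** Shrinkage occurs with some participants continuing (A) and with nobody continuing (B, D). The change is untouched when activity and outcome are unrelated (C), and it grows when activity rises after the programme (F). What decides the result is the product g × d, not who continues.

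**The case against.** **It is loose wording for sport activities.** This is plausible. Three other places name sport activities, and section 2.5 has their changes recorded. On that reading the self-adjustment goes away. But physical activity is the heading of a defined outcome in 2.7.3, and an analyst following 2.11.3 would enter the IPAQ score. Section 2.10 repeats the recording of sport activities for the baseline and intervention periods but not for follow-up, so the text does not settle the matter.

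**Nobody would publish a model of a variable on itself.** Probably true: the perfect fit would show at the first run. The covariate sentence is generic, and falls already have their own test in 2.11.4, so it may not be meant mechanically for every outcome. This lowers the risk of a wrong report. It leaves the model for physical activity to be chosen after the data are seen.

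**Change net of activity is a legitimate question.** It is, particularly in a single-group study that wants to separate out other activity changes. That is a reason to keep it as a secondary view. It is not the question 2.11.3 states.

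**Stronger readings.** A reader might infer that adjustment necessarily hides a loss of benefit, or that it does so only if some participants continue the programme and the loss follows stopping. Neither is supported: scenario F enlarges the change, and B and D shrink it with nobody continuing. A reader might also want a percentage of bias. The document gives no activity shift, no association between activity and outcome, and no share of continuers, so any percentage would only restate assumptions.

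**Conclusion.** Wrong as written, and a minor-to-moderate correction.

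The first part needs no assumption beyond a literal reading of 2.11.3: the adjusted T3-T4 change in physical activity is zero by construction. The second part holds whenever mean activity shifts between T3 and T4 and activity is associated with the outcome: the coefficient is then not the total change. Its size and direction cannot be given from the document, and the simulated values only illustrate that it can go either way.

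The defect is confined to the T3-T4 models. The effect of the programme at T3 (2.11.2) does not use this covariate, and the McNemar comparison of fallers (2.11.4) uses no covariates, so neither is affected. If sport activities were meant, what remains is an inconsistency of terms, plus the question of whether continued training would count as sport activity.

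**What to change.** Rewrite the covariate sentence in 2.11.3 so that:

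- physical activity never enters its own model;
- for the other outcomes, the main T3-T4 model leaves out IPAQ physical activity and keeps medication use;
- if recorded changes in sport activities were intended, as in 2.11.2, they are named as such, and continued PRET is not counted among them;
- an activity-adjusted model for the other outcomes is shown only as a sensitivity analysis, labelled as change net of concurrent activity.

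The cost is one sentence and one extra model per outcome. If the sport-activities option is taken, the study also needs to know who continued PRET during follow-up: one yes/no item at T4 if it is not already recorded. Visits and participant rules do not change. The downside is that the main T3-T4 estimate no longer adjusts for other changes in activity; the sensitivity analysis covers that.
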